**Fig. 1 Fig1:**
[figure not shown]
Consolidated Standards of Reporting Trial (CONSORT) guidelines flow diagram for enrolment and randomisation in the Cardiometabolic HIIT-RT Study

#### Intervention

The participants who are randomly assigned to the intervention group will participate in the cardiometabolic programme.Usual clinical care group

This group will receive usual clinical care according to the consensus recommendations of the national goals for cardiovascular health promotion and disease reduction of the American Heart Association [31] and Colombian guidelines COLDEPORTES (in Spanish, Departamento Administrativo del Deporte, la Recreacion, la Actividad Fisica y el Aprovechamiento del Tiempo Libre) [32]. Participants will receive counselling about goals for cardiovascular health, as well as monitoring cardiovascular health over time in the Colombian population, key signs and symptoms, diet and screening for cardiometabolic risk factors. This group will be asked to maintain their level of activity during the 12-week study period.2.High-intensity interval training (HIIT) group

The HIIT protocol will be completed with fast walking or running on a treadmill with the deck inclined to reach the desired intensity. We will calculate the training energy expenditure for participants’ age ranges associated with meeting the consensus public health recommendations from the WHO [16] and the US Department of Health and Human Services [17]. Each preparatory period starts with an exercise dose of 6 kcal kg^-1^ week^-1^, which will increase progressively by 2 kcal kg^-1^ week^-1^ until week 4, where it will remain at 12 kcal kg^-1^ week^-1^ for weeks 5 to 12.

*Preparatory training phase: weeks 1–4*

To initiate our study we will use a 4-week preparatory phase of training to bring all participants up their 300-kcal goal for the session. To accomplish this they will warm up at 65 % of maximum heart rate (HRmax) (5 min); exercise for 4 × 4-min intervals at 60–80 % HRmax, interspersed with a 4-min recovery period at 55 % HRmax, at a frequency of three times per week.

*Protocol of interval training: weeks 5–12*

The overall goal for the HIIT group is to perform exercise sessions in 4 × 4-min intervals at 85–95 % HRmax (with the target zone maintained for at least 2 minutes), interspersed with a 4-min recovery period at 65 % HRmax. During each exercise session, participants will adhere to the 12-kcal kg^-1^ week^-1^ energy expenditure format, equivalent to 500 kcal of expended energy at the end of training and cool-down (5 min), with a range total exercise time of 35 to 45 min (Fig. 2). Exercise will be performed for three sessions per week. During the supervised intervention, we will record HR using an HR monitor (Polar Pacer, Lake Success, NY, USA) to ensure compliance with the exercise stimulus at the predetermined target HR zone. In addition, HR and Borg ratings will also be measured in each exercise session.

**Fig. 2 Fig2:**
[figure not shown]
Example of a 30–40-min 4 × 4 high-intensity interval training (HIIT) session

**Fig. 3 Fig3:**
[figure not shown]
Schedule of enrollment, intervention and assessment*

3.Resistance training group

*Preparatory training phase: weeks 1–4*

All participants will complete a base resistance training protocol during the 2 weeks prior to the training intervention (Table 2). This phase will encompass a total of three workouts (Monday, Wednesday, and Friday) during the 4 weeks. During the adaptation phase, the subjects will expend energy up to 300 kcal at 20–50 % of one repetition maximum (1RM), for 2 × 20–30 repetitions with 1-min rest intervals. During each exercise session, participants will adhere to the 6–8 kcal kg^-1^ week^-1^ energy expenditure format. The purpose of the preparatory phase will be to instruct proper lifting technique, familiarise participants with all exercises, and ensure that the participants began the study with a comparable training base.

**Table 2 Tab2:** Resistance training programme

Programme variable	Preparatory phase	Volume	Intensity
Preparatory training phase			
Exercise prescription	20–40 % 1RM	40 % 1RM	30–50 % 1RM
Training intensity	2 × 20–30 repetitions	2 × 20–30 repetitions	2 × 20–30 repetitions
Training volume	1 min	30 s	1 min
Energy expenditure	300 kcal		
Rest time	Weeks 1 to 4		
Specific exercises			
Barbell squats			
Split squats			
Biceps curls			
Dumbbell lateral raises shoulder			
Dumbbell military shoulder press			
Dumbbell triceps curls			
Resistance training protocol			
Exercise prescription	40–60 % 1RM	70 % 1RM	70–80 % 1RM
Training intensity	4 × 20–30 repetitions	4 × 20–30 repetitions	4 × 20–30 repetitions
Training volume	1 min	30 s	1 min
Energy expenditure	500 kcal		
Rest time	Weeks 1 to 4		
Specific exercises			
Barbell squats			
Dumbbell squats adductor			
Split squats			
Lateral adductor squat			
Biceps curls			
Dumbbell lateral raises shoulder			
Dumbbell military shoulder press			
Dumbbell triceps curls			

Volume = sets × repetitions. *1RM* one repetition maximum

*RT protocol: weeks 5–12*

After the preparatory phase, participants will expend 500 kcal of energy during the protocol training phase at 40–80 % of 1RM, for 4 × 20–30 repetitions and 1-min rest intervals. The RT protocol will be used to complete a resistance circuit (including upper and lower muscle groups; eight exercises); all participants will expend energy up to the 500-kcal goal. The entire workout will last approximately 30–40 minutes, depending on the number of exercises (Table 2), at a frequency of three times per week. Each session is preceded and followed by a gradual warm-up and cool-down period (both of 10-min duration and consisting of walking and light, static stretching (avoiding muscle pain) in most muscle groups). The cool-down period also includes relaxation and stretching exercises. The RT protocol will be performed through the full range of motion normally associated with correct technique for each exercise, engaging the major muscle groups (abdominal, dorsal, shoulder, upper and lower limb muscles). As a general rule and to avoid potential risks, we will avoid (1) activities that include Valsalva’s mechanism, (2) ballistic and plyometric movements, and (3) positions of extreme muscular tension. This resistance training programme has been used before, successfully promoting strength and muscle gains in middle-aged and elderly populations with a variety of conditions (e.g. diabetes type II and obesity) [33, 34].4.Combined training group

This group will receive both the HIIT and RT protocols as described above. Therefore, the energy expenditure associated with the physical training prescribed for the vigorous-intensity group will be approximately 1500 kcal/week.

Overall, we will monitor each subject’s HR (FS1, Polar Electro Öy, Kempele, Finland) during the exercise sessions. We will estimate the energy expenditure during the exercise sessions by calibrating the energy expenditure to the HR during the VO_2_max tests performed at the baseline and post-intervention time points. The regression of the energy expenditure will be calculated for each participant according to HR and minutes spent exercising during the training sessions. Trainers will be physical therapists and physical educators with experience developing and monitoring exercise programmes among clinical populations. All protocol training will be performed under observation and supervision in an exercise laboratory with complete and strict monitoring of the amount of exercise completed in each session. Adherence to the exercise programme will be encouraged by the exercise professional who supervises each of the group sessions. To maximise adherence to the training programme each session will have a maximum of three to five participants training simultaneously. Attendance at supervised sessions includes compliance with target HR and expenditure energy and will be monitored and recorded by research staff. Each participant will meet with the study dietician for nutrition assessment and counselling, and an individualised nutrition intervention plan will be developed from the baseline food intake assessment according to participant preferences [35]. This plan is a standardised meal consisting of 1300 to 1500 kcal (50–55 % carbohydrates, 30–35 % total fat, less than 7 % saturated fat and 15–22 % protein).

At the beginning of the training protocol, we will obtain the participants’ weight to determine weekly energy expenditure necessary to achieve their target of 12 kcal kg^-1^ week^-1^ (iso-energetic). It is expected that the gradual increase in total energy expenditure will minimise fatigue, soreness, injuries, and attrition.

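### The stated training energy doses contradict each other, leaving the combined arm's weekly dose open by a factor of two (1500 or 3000 kcal)

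*Protocol article*

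**What the plan says.** All statements are in the protocol article, mostly under Intervention.

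- **HIIT, weeks 1–4.** The dose starts at 6 kcal/kg/week and rises by 2 each week "until week 4, where it will remain at 12 kcal kg^-1^ week^-1^ for weeks 5 to 12". The preparatory sessions, three a week, have a fixed goal: "we will use a 4-week preparatory phase of training to bring all participants up their 300-kcal goal for the session".
- **HIIT, weeks 5–12.** Here "participants will adhere to the 12-kcal kg^-1^ week^-1^ energy expenditure format, equivalent to 500 kcal of expended energy at the end of training". The frequency is unchanged: "Exercise will be performed for three sessions per week".
- **RT, weeks 1–4.** Sessions go up to 300 kcal, three a week, under a 6–8 kcal/kg/week format. Table 2 lists 300 kcal without qualification.
- **RT, weeks 5–12.** Each session has a 500-kcal goal, three times a week. The Abstract likewise describes the circuit as repeated until 500 kcal has been spent.
- **Combined arm.** "This group will receive both the HIIT and RT protocols as described above". The next sentence draws the consequence that "the energy expenditure associated with the physical training prescribed for the vigorous-intensity group will be approximately 1500 kcal/week".
- **Common target.** Weight is taken at the start of training "to determine weekly energy expenditure necessary to achieve their target of 12 kcal kg^-1^ week^-1^ (iso-energetic"). No training arm is excepted.

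Study design and setting calls the trial a 2 × 2 factorial. Statistical analyses plans a comparison of the four groups and, last, an interaction between HIIT and RT on the primary outcome.

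**The concern.** The protocol gives the training dose in two currencies, kcal per session and kcal per kg per week, and treats them as interchangeable. It also gives the combined arm a weekly total equal to that of one modality alone, while prescribing both modalities without any stated reduction or split.

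What is at stake is the definition of the intervention. If the combined arm does both protocols in full, it trains at twice the energy dose of either single arm, and a combined-versus-RT or combined-versus-HIIT difference reflects added volume as well as added modality. If the total is held at about 1500 kcal/week, the combined cell does not carry the full single-arm dose of both modalities. The main effects and interaction would then not be those of HIIT and RT as given alone. Trainers working from this text could deliver either.

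**Working it through.** Inputs are the session goals, frequencies and per-kg doses listed above. W is body weight in kg, measured at the start of training, so it is fixed for setting the target. At three sessions a week, the per-kg dose d corresponds to d × W / 3 kcal per session.

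**1. The 1500 kcal/week figure (independent of weight)**
- HIIT alone: 500 × 3 = 1500 kcal/week.
- RT alone: 500 × 3 = 1500 kcal/week.
- Both in full: 1500 + 1500 = 3000 kcal/week, twice the stated figure.

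The stated 1500 can be reached for the combined arm in two other ways, and neither fits the rest of the text:
- One 500-kcal dose shared by the two modalities, three times a week, gives 1500. That is not both protocols as described.
- 12 + 12 = 24 kcal/kg/week gives 1500 only at 1500 / 24 = 62.5 kg, and then each modality supplies 12 × 62.5 / 3 = 250 kcal per session, not 500.

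**2. HIIT, week 4 against weeks 5–12 (independent of weight)**
- Ramp: 6, 8, 10, 12, so 12 kcal/kg/week is reached in week 4.
- Week 4: 12 × W / 3 = 300 gives W = 75 kg.
- Weeks 5–12: 12 × W / 3 = 500 gives W = 125 kg.

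The per-kg dose and the frequency stay the same while the session goal rises by two thirds (500 / 300 = 1.67). No single W satisfies both lines.

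**3. Per-kg dose against fixed session dose (dependent on weight)**

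12 kcal/kg/week equals 1500 kcal/week only at 1500 / 12 = 125 kg. The documents give no mean weight, so the weights below are assumptions.

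| W (kg, assumed) | 12 × W (kcal/week) | per session | 500 / per session |
|---|---|---|---|
| 70 | 840 | 280 | 1.79 |
| 80 | 960 | 320 | 1.56 |
| 100 | 1200 | 400 | 1.25 |
| 125 | 1500 | 500 | 1.00 |

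Reading 500 kcal as a weekly total, or 12 kcal/kg as a session dose, does not help: either implies 500 / 12 = 41.7 kg.

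**4. RT, weeks 1–4 (dependent on weight)**

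300 × 3 = 900 kcal/week. This equals 6 kcal/kg/week at 900 / 6 = 150 kg and 8 kcal/kg/week at 900 / 8 = 112.5 kg. If 300 kcal is only a ceiling, as the running text may intend, lower weights are compatible with it. If it is the dose, as Table 2 lists it, they are not. Over the same four weeks, with the same 300-kcal figure, HIIT climbs to 12 kcal/kg/week.

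**The case against.** Several points on the other side are sound.

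- **Iso-energetic is attached to the per-kg target, not to 1500 kcal/week.** It may mean an equal dose per kg across participants. A reader might infer that the trial must be either not iso-energetic or not a 2 × 2 factorial. The documents do not support that, because nowhere do they say that the combined arm is volume-matched to the single arms. The Background's remark on comparable amounts concerns HIIT and RT. This objection stands.
- **The 1500 kcal/week sentence may be mislabelled or misplaced.** Its group name belongs to no arm, and 1500 is exactly the HIIT arm's 3 × 500. This stands in part: its position under the combined arm and its opening *Therefore* point to that arm. If it does describe HIIT, the combined total is stated nowhere, and the common 12 kcal/kg/week target still sits beside two full protocols with no exception made.
- **Extra volume in the combined cell is inherent in a factorial.** A cell that receives both factors in full receives more exercise. That is not a defect, and the hypothesis does not promise volume matching. This stands; the consequence only needs to be stated.
- **The four-group comparison is already planned, and the protocol admits low power for the interaction.** This stands. Comparisons with usual care remain possible under either reading, so there is no ground for requiring the factorial label to be dropped.

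None of this removes the conflicts in steps 1 and 2. Nor are they detail that an article leaves to a fuller document: the figures are printed, and they disagree.

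**Conclusion.** The energy prescription is internally contradictory and cannot be followed as written. Two conflicts rest on the protocol's own figures alone: 3000 against 1500 kcal/week in the combined arm, and a 300-kcal against a 500-kcal session at the same 12 kcal/kg/week in HIIT. The first assumes only that both protocols are given without reduction, which is what the text says. The second assumes only that the 300-kcal goal applies in week 4.

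The per-kg mismatch is real except at 125 kg, but its size (79 % to 25 %) rests on assumed weights of 70 to 100 kg. The RT preparatory mismatch is the weakest part, since it depends on whether 300 kcal is a dose or a ceiling.

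The consequence is limited to interpretation of the combined arm and the interaction. It does not show that the factorial design is invalid or that the combined arm is improperly confounded. No view is taken on which dose is right.

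**What to change.** 1. Under Intervention, reconcile the HIIT text (both phases), the RT text with Table 2, the combined-arm text and the closing paragraph on the weekly target, so that each arm has one consistent energy prescription. The choice is the sponsor's.
2. State which arm the 1500 kcal/week describes, and whether iso-energetic means across participants or across arms.
3. Align Study design and setting and Statistical analyses with the result:
   - If both protocols are given in full, state that combined-versus-single contrasts are not volume-matched.
   - If the total is shared, state that the combined cell does not carry the full single-arm dose of either factor, so the main effects and interaction are not those of HIIT and RT as given alone. Rest conclusions on the four-group comparison already planned.
4. Report achieved kcal/week by arm. Recruitment had already begun when the article was written, so also say which prescription the trainers have been following.

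The cost is a protocol clarification and a few sentences of analysis text. Energy expenditure in supervised sessions is already monitored and recorded, so no new data collection is needed.

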### Data collection and outcome measures

Outcome measures will be assessed at baseline and at 12-week follow-up by personnel blinded to the treatment allocation. Data will be recorded on standardised forms and entered into a secured-access database that contains quality control checks (e.g. range checks, notification of missing data).

The primary outcome measure is endothelial function as measured by flow-mediated dilatation (FMD). The secondary outcome variables include HR variability, pulse wave velocity (PWV), weight, BMI, WC, body composition, body temperature, biochemical profile, health-related physical fitness, self-perceived health, health-related quality of life (HRQL), and side effects. Other variables of interest include 24-hour dietary recall, lifestyle and demographic characteristics (Table 3 and Figure 3).

**Table 3 Tab3:** Summary of time point measurements of the primary and secondary outcomes of the study

Type of outcomes	Specific outcomes	Measurements		
		1-baseline (week 0)	2-moment (week 4)	3-moment (week 12)
Primary outcomes	Endothelial function as measured by flow-mediated vasodilatation	X		X
Secondary outcomes	Vascular function: heart rate variability, aortic pulse wave velocity, augmentation index and blood pressure	X		X
	Morphological component: weight, height, BMI, waist circumference	X	X	
	Body composition: fat mass and non-bone lean body mass	X		X
	Body temperature	X		X
	Plasma samples and biochemical analysis: LDL cholesterol (LDL-c), HDL cholesterol (HDL-c), total cholesterol, triglycerides, glucose, glycated haemoglobin (HbA1c)	X		X
	Fitness component: self-reported fitness, 1RM, hand-grip and peak uptake of volume of oxygen	X		X
	Self-perceived health: health-related quality of life	X		X
	Recent Physical Activity Questionnaire	X	X	X
	Demographic information	X		
	Side effects	X	X	X

*1RM* one repetition maximum, *BMI* body mass index

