##### Morphological component

Anthropometric variables will be assessed by a nutritionist in accordance to the International Society for the Advancement of Kinanthropometry (ISAK) guidelines [43]. Variables will be collected at the same time in the morning, between 00.70 and 00.80 hours, following an overnight fast of at least 10–12 hours. The body weight of the subjects will be measured when the subjects are in underwear and without shoes, using electronic scales (Tanita® BC544, Tokyo, Japan). The height of the subjects will be measured using a mechanical stadiometer platform (Seca® 274, Hamburg, Germany). The BMI of the subjects will be calculated as the body weight in kilograms divided by the square of the height in metres. The WC will be measured as the narrowest point between the lower costal border and the iliac crest; in case this is not evident, it will be measured at the midpoint between the last rib and the iliac crest using a tape measure (Ohaus® 8004-MA, Parsippany, NJ, USA). The waist-to-height ratio will be computed by dividing WC by height, and this provides a surrogate measure of central body fat. We will take each measure twice and use the average measure obtained, unless the first and second measures vary by more than 1 %, in which case we will use the median of three measurements.

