##### Health-related physical fitness

Physical fitness will be measured using tests that have previously shown high validity and reliability levels. It will be determined using a maximum treadmill exercise test (Precor TRM 885, Treveso, Italy) following the modified Balke protocol [49], which has been extensively used [50, 51] and validated [52]. The treadmill test will use a ramp protocol where the inclination is constant (5.5 %) and the speed increased by 0.5 km/h every minute, starting at 4 km/h. Each session will begin with a 5- to 10-min warm-up at 50 W. We will ask participants to refrain from smoking for 2 hours before the test, and from drinking alcohol or doing any vigorous- or moderate-intensity activities for 48 h before the test. HRmax will be used to determine the training intensity for each participant. We will measure blood pressure prior to and during the test. Exercise will be terminated if participants are fatigued, or earlier if they fulfill the ACSM’s guidelines for ‘Indications for Terminating Exercise Testing’ [53]*.* CRF is defined as the highest recorded VO_2_ value (VO_2_max) after two of three criteria are met: (1) a plateau in VO_2_ after increase in workload, (2) a respiratory exchange ratio >1.10, and (3) a maximal HR within 10 bpm of their age-predicted maximum. Muscular fitness will be assessed using the hand-grip test (maximum hand-grip strength assessment) using a standard adjustable handle analogue hand-grip dynamometer T-18 TKK SMEDLY III® (Takei Scientific Instruments Co., Ltd, Niigata, Japan). Participants will be given a brief demonstration and verbal instructions for the test and, if necessary, the dynamometer will be adjusted according to the subject’s hand size according to predetermined protocols. Hand-grip strength will be assessed with the subject in a standing position with their shoulders adducted and neutrally rotated, and their arms parallel but not in contact with their body. The participants will be asked to squeeze the handle for a maximum of 3–5 s, but no verbal encouragement will be given during the test. Two trials will be allowed in each limb, and the average score will be recorded as peak hand-grip strength (kg). Thus, the values of hand-grip strength presented will combine the results of left- and right-handed subjects, without consideration of hand dominance. Hand-grip will be adjusted by allometric parameters defined by Jaric [54] (dynamometry/weight^0.67^). Strength in the eight exercises will be assessed at baseline and immediately after the intervention ends. A general warm-up consisting of riding a cycle ergometer for 5 min at a self-selected resistance will precede strength testing. Standardised procedures will be used to predict a one-rep max (1RM) from reps-to-fatigue barbell squats, dumbbell adductor squats, split squats, lateral adductor squat, biceps curls, dumbbell lateral shoulder raises, dumbbell military shoulder press, and dumbbell triceps curls from each participant’s performance during the preparatory training phase [55]. Progressive overload will be achieved by increasing the load when all prescribed repetitions (for a particular exercise) are achieved on two consecutive workouts [56].

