#### Statistical analyses

The final data will be analysed using IBM SPSS 22.0 (SPSS, Inc., Chicago, IL, USA) and SAS software (SAS Institute Inc., Cary, NC, USA). An exploratory analysis will be performed to determine the frequency, range, variability, and distribution type for each variable to use the most appropriate statistical test when comparisons will be necessary. These analyses permit the assessment of the primary analysis of the data and will be undertaken using the principle of intention-to-treat (ITT). The ITT analysis for this study will include all participants, including those who are not fully compliant and those with missing outcome data. Because this is an experimental design with two measures of the primary and secondary outcomes, the first at baseline x0 (t0 = weeks) and the second after interventions x1 (t1 = 12 weeks) in four study groups, a comparative analysis between these measures to establish differences will be executed. To perform these comparisons, one-way ANOVA or Kruskal-Wallis tests will be applied when appropriate. Subsequently, a multivariate analysis will be carried out, and the autocorrelation between repeated measures will be taken into account. We will use longitudinal analysis methods, such as a generalised estimating equation approach, to control the differences among measures at baseline and to incorporate incomplete observations into this analysis. Finally, we will investigate if there is an interaction between the two interventions for the primary outcome at 12 weeks of supervised training HIIT, RT or combined training (HIIT + RT). For these analyses, we will include appropriate interaction terms in the models [38, 65]. The trial is not powered to detect these interactions and is likely to have poor precision for the interaction terms. We plan to report regression coefficients for the interaction terms and their 95 % confidence intervals. However, we aim to recruit 15 participants per group (a total of 60) to accommodate for a 20 % attrition rate and elimination due to non-compliance.

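### Table 3 schedules weight, height, BMI and waist circumference at weeks 0 and 4 but not at week 12, against the protocol's own text and analysis

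*Protocol article*

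**What the plan says.** Three places in the protocol article bear on when anthropometry is measured.

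- **Data collection and outcome measures, text.** The general rule is "Outcome measures will be assessed at baseline and at 12-week follow-up by personnel blinded to the treatment allocation". No outcome is exempted. The next paragraph lists the secondary outcomes: "The secondary outcome variables include HR variability, pulse wave velocity (PWV), weight, BMI, WC, body composition, body temperature, biochemical profile", followed by fitness, self-perceived health, quality of life and side effects.
- **Table 3.** The row "Morphological component: weight, height, BMI, waist circumference" has a mark at baseline and at week 4, and none at week 12.
- **Statistical analyses.** The comparison is set up in these terms: "Because this is an experimental design with two measures of the primary and secondary outcomes, the first at baseline x0". The second measure is placed at 12 weeks, in all four groups.

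The Morphological component section describes technique, time of day and fasting state, but gives no study week. Figure 3, the schedule of assessments, is not shown in the text available here.

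**The concern.** Table 3 summarises which measurement is taken at which visit. As printed, it gives weight, BMI and waist circumference no end-of-training value, while the text and the analysis both depend on one.

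If the table were followed, the value would be missing for every participant. The generalised estimating equations in the Statistical analyses section can use incomplete records, but they cannot supply a time point at which nobody was measured. The week-4 value is no substitute, because it falls at the end of the preparatory phase. For HIIT, the sessions described as "The overall goal for the HIIT group is to perform exercise sessions in 4 × 4-min intervals at 85–95 % HRmax" belong to weeks 5 to 12. Under the RT text, the 500-kcal sessions also come after the preparatory phase. A week-4 difference would therefore not measure the 12-week effect that the trial sets out to compare.

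One further outcome depends on a week-12 weight. The Health-related physical fitness section states "Hand-grip will be adjusted by allometric parameters", with the formula "dynamometry/weight^0.67", and Table 3 schedules hand-grip at week 12. No weight is scheduled at that visit.

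**Working it through.** This is a check of one schedule against another, so there is no figure in the plan to reproduce.

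**Step 1. Is the blank cell an extraction fault?** The rows of Table 3 read as follows.

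| Row | Week 0 | Week 4 | Week 12 |
|---|---|---|---|
| FMD (primary) | X | | X |
| Vascular function | X | | X |
| Morphological component | X | X | |
| Body composition | X | | X |
| Body temperature | X | | X |
| Plasma samples | X | | X |
| Fitness | X | | X |
| Self-perceived health | X | | X |
| Physical activity questionnaire | X | X | X |
| Demographic information | X | | |
| Side effects | X | X | X |

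Rows on both sides of the morphological row keep their empty week-4 cell and their week-12 mark, and two rows carry all three marks. The columns have survived, so the blank is very unlikely to come from text extraction.

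**Step 2. How many rows and outcomes are affected?** Leaving out demographics, which are properly baseline only, there are 10 outcome rows. Week 12 is marked in 9 and blank in 1.

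The text lists 12 secondary outcomes: HR variability, pulse wave velocity, weight, BMI, waist circumference, body composition, body temperature, biochemical profile, physical fitness, self-perceived health, quality of life and side effects. Three of them sit in the affected row. Height is in the table row but is not a named outcome.

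**Step 3. How much training follows the last scheduled value?** Week 4 leaves 12 − 4 = 8 of 12 weeks. At three HIIT sessions a week, that is 3 × 4 = 12 sessions before and 3 × 8 = 24 after, so 24/36 = 67 % of sessions come after the last measurement. These 24 include every session at 85–95 % HRmax. The same count fits RT if its preparatory phase also has three workouts a week.

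**Step 4. What would happen to adjusted hand-grip?** Suppose week-12 grip were divided by week-4 weight for want of a later one. If weight falls by a fraction p after week 4, the ratio of this value to the correct one is (1 − p)^0.67. The protocol gives no expected weight change, so p is an assumption.

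- p = 0.01: 0.99^0.67 = 0.9933, or 0.7 % too low.
- p = 0.02: 0.98^0.67 = 0.9866, or 1.3 % too low.
- p = 0.05: 0.95^0.67 = 0.9662, or 3.4 % too low.

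These figures only illustrate scale. The protocol does not propose this substitution.

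**The case against.** The strongest reply is that the governing text already settles the matter. It calls for 12-week assessment without exception, the analysis section repeats it, and Table 3 is only a summary. On that view this is a one-cell clerical slip. Harm follows only if staff work from the article's table rather than from the operations manual or Figure 3, neither of which is shown. It is fair to say that actual loss of data has not been demonstrated, and that a misplaced mark is the likely cause. The table is nevertheless a measurement schedule, and no unseen document can make it agree with the text beside it.

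Several narrower objections stand and limit the point.

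- **DEXA.** The week-12 scan gives fat and lean mass, from which body weight, and so BMI, could be approximated. Waist circumference could not be recovered, and the protocol specifies scale weight.
- **BMI.** In adults of fixed height, BMI carries the same information as weight. The three outcomes rest on two lost measurements.
- **Waist-to-height ratio.** The protocol says "The waist-to-height ratio will be computed by dividing WC by height", but gives no study week and does not list the ratio as an outcome. It adds little support.
- **RT sessions.** The wording of the RT preparatory phase is unclear. It mentions both 2 weeks and 4 weeks, and Table 2 prints weeks 1 to 4 under the 500-kcal protocol as well. The 12-and-24 split is firm for HIIT and is one reading for RT.

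**Conclusion.** The concern holds. Table 3 contradicts the outcome text and the Statistical analyses section on when weight, BMI and waist circumference are measured. One of 10 outcome rows and 3 of 12 listed secondary outcomes are affected directly, and hand-grip adjusted for weight is affected as a derived value. Followed literally, the table leaves no 12-week waist circumference or scale weight for any participant, and no follow-up value after the first 4 of 12 weeks.

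The contradiction rests only on the printed table and text. The practical loss depends on whether assessors follow the table, which cannot be known from the article. No direction of bias is claimed. The primary outcome and the sample size, both based on FMD, are untouched. The point should be corrected, but it does not threaten the main result.

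**What to change.** In the morphological row of Table 3, mark week 12. Keep the week-4 mark only if an interim value is wanted, for example to set the weight-based dose for weeks 5 to 12. Use week 12 as the analysis time point for weight, BMI and waist circumference, as the text already implies, and confirm that Figure 3 and the operations manual show the same. The physical activity and side-effects rows already include weeks 0 and 12 and need no change.

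The cost is one mark in one row. If 12-week anthropometry is not already being done, it adds scale and tape measurements at a visit that takes place anyway. The correction should come before the first participants reach week 12, because a missed measurement cannot be collected afterwards.
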